# **Secondary endpoint**

## **Optimal therapy within 48hrs of positive culture**

This endpoint will be analysed in the same way as the primary endpoint.

Where the endpoint is Unknown and the patient was discharged <24 hours after admission, the endpoint should be changed considered not optimal unless recorded as optimal.

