# **Analysis population and definition of baseline**

The main population for all analyses is the population of all subjects for which the primary endpoint could be defined by the endpoint review committee (modified intention-to-treat). All analyses will be according to the randomized diagnostic arm.

The following participant will be excluded from the modified intention-to-treat population:

- Patients who discharged or died before the culture flagged positive (DISCHARGE.DischargeDate + DISCHARGE.DischargeTime before SAMPLE.GDetectedDate + SAMPLE.GDetectedTime).
- Patients where the endpoint review committee felt the culture was not in itself enough to guide therapy (e.g. potential contaminant, viridans strep in a patient without signs of endocarditis),.

Baseline is defined as the time point when the participant’s first culture flagged positive.

All patients excluded from the modified intention to treat population and reasons for exclusion will be summarized by diagnostic arm (“MALDITOF MS” or “ROUTINE DIAGNOSTICS”).

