# **Primary endpoint: proportion of patients on optimal antibiotic treatment within 24 hours of positive culture (first growth of an eligible specimen)**

## **Derivation**

A patients is defined to be on optimal antibiotic treatment within 24h of positive culture (first growth of an eligible specimen) according to the endpoint committee.

As a conservative measure, patients in the modified intention-to-treat population who withdrew or died within 24 hours of positive culture will be classified as not being on optimal antibiotic treatment by 24 hours unless the optimal antibiotic treatment was already started while the subject was still in the study and alive, similarly those where the endpoint committee judged that they could not classify the outcome as the organism was not the only reason for antimicrobial therapy will be classified as not being on optimal therapy.

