## **Planned analysis**

The number (%) of patients receiving the optimal antibiotic treatment within 24 hours of positive culture will be described by diagnostic arm overall and in pre-defined subgroups (see below).

For the formal comparison between the two diagnostic groups, we will use a logistic regression model of the primary endpoint depending on the treatment groups, with additional adjustment for the first specimen type (blood vs. other) and the hospital. The main effect measure is an odds ratio of optimal antibiotic treatment within 24 hours between treatment groups and a corresponding two-sided 95% confidence interval (CI) and p-value. P-values ≤0.05 are considered significant.

The analysis will be implemented using the R function glm.

The reasons why subjects were not on optimal antibiotics therapy within 24 hours will be summarized descriptively as frequency of reasons (%) amongst patients without optimal treatment.

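### The rule for Unknown 48-hour outcomes uses a different clock and window from the endpoint, so some early discharges are left unclassified

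*SAP*

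**What the plan says.** - **Endpoint.** The section heading is "Optimal therapy within 48hrs of positive culture". The first sentence under it reads "This endpoint will be analysed in the same way as the primary endpoint".
- **Rule for Unknowns.** The same section continues: "Where the endpoint is Unknown and the patient was discharged <24 hours after admission, the endpoint should be changed considered not optimal", with the exception "unless recorded as optimal".
- **Time zero and population.** In *Analysis population and definition of baseline*, the sentence starting "Baseline is defined as the time point when the participant" ties baseline to the first positive flag, not to admission. The same section removes from the modified intention-to-treat (mITT) population "Patients who discharged or died before the culture flagged positive".
- **Parallel rule at 24 hours.** In the primary endpoint's *Derivation*, mITT patients "who withdrew or died within 24 hours of positive culture will be classified as not being on optimal antibiotic treatment by 24 hours", unless optimal treatment had already started. That rule counts from positive culture, and its window equals the endpoint's.
- **Model.** The primary endpoint's *Planned analysis* specifies logistic regression: "The analysis will be implemented using the R function glm".
- **Time to optimal treatment from first growth.** Patients discharged without optimal treatment have a competing event at discharge. The model treats them as never having received it.

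**The concern.** A rule for outcomes that cannot be observed should cover the patients who leave before the endpoint's window closes. Here the window closes 48 hours after positive culture, but the rule asks whether the patient left within 24 hours of admission. No optimal-therapy endpoint in the SAP starts at admission.

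At stake is the denominator of the 48-hour comparison. Unknown outcomes that the rule does not reach have no stated handling. A default model fit would omit them silently, although the SAP's approach elsewhere is to count such patients as not optimal. The sentence is also hard to program: an endpoint that is Unknown cannot at the same time be recorded as optimal, so the exception needs a definition.

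**Working it through.** The SAP gives no figure on this point, so there is none to reproduce. The check is a comparison of time axes, followed by an illustration on assumed inputs.

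**1. Definitions.** Let A = admission, F = culture flag and D = discharge. Then D − A = (D − F) + (F − A).

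- mITT condition (*Analysis population*): D ≥ F.
- Rule as written (48-hour section): D − A < 24 h.
- Set matching the endpoint's clock and window: D − F < 48 h.

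**2. Who the rule can reach.** Take F ≥ A, a culture that flags after admission. Both terms on the right are then non-negative, so D − A < 24 h forces F − A < 24 h and D − F < 24 h. Three results follow without any assumed data:

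- Nobody discharged 24 to 48 hours after growth can meet the rule, yet this is the interval that separates this endpoint from the primary one.
- Nobody whose culture flags 24 hours or more after admission can meet it, however soon they then leave.
- The omitted group is exactly D − F < 48 h with D − A ≥ 24 h.

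Example: a culture flags on hospital day 5 (F − A of at least 4 × 24 = 96 h) and the patient leaves 30 h later. D − A is at least 96 + 30 = 126 h, so the rule does not apply, although the patient left 48 − 30 = 18 h before the window closed.

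**3. What happens to an omitted Unknown.** The mITT requires only that the *primary* endpoint could be defined, so a patient can be in the population with an Unknown 48-hour outcome. With no rule to classify it, the outcome is missing, and glm in R omits it by default. If optimal within 24 hours implies optimal within 48, such a patient was not optimal at 24 hours. The same person is then a failure in one analysis and absent from the next.

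**4. Effect on a proportion.** Let u be the fraction of an arm with an omitted Unknown outcome and p the proportion optimal among the rest. Dropping these patients reports p. Counting them as not optimal reports (1 − u)p. The gap is u × p, which cannot exceed u. The SAP gives neither quantity.

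**5. Illustration of reach (assumed inputs).** Independent log-normal times were simulated: admission to flag with median 12 to 48 h (log-SD 0.5), and length of stay with median 5 to 15 days (log-SD 0.9), keeping patients discharged after the flag. Selected settings:

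| Median A to F | Median stay | Meets rule (% of mITT) | D − F < 48 h (% of mITT) | Share of the latter reached |
|---|---|---|---|---|
| 12 h | 5 d | 2.717 | 21.84 | 12.44% |
| 12 h | 15 d | 0.106 | 2.5 | 4.23% |
| 24 h | 10 d | 0.168 | 8.83 | 1.9% |
| 48 h | 5 d | 0.138 | 28.38 | 0.49% |
| 48 h | 15 d | 0.005 | 6.01 | 0.09% |

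Over the whole grid the rule reaches about 0.1% to 12% of patients discharged within 48 hours of the flag. These are shares of all such discharges. The share with an Unknown outcome is not known.

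**The case against.** **Other handling may already cover many of these patients.** Analysing the endpoint like the primary one may carry over the primary derivation's conventions. Deaths, withdrawals and outcomes unclassifiable because the organism was not the sole reason for therapy would then already count as not optimal. This stands, and it narrows the gap to patients discharged alive whose outcome is Unknown for some other reason. It does not close the gap, because those conventions do not name discharge.

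**The intended window is not stated.** This also stands. A window of 48 hours from culture is inferred from the endpoint's title and the pattern of the 24-hour rule. What the text itself shows is the mismatch.

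**Stronger readings that the SAP does not support.**

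- A reader might infer that the primary endpoint has the same hole, since its rule names death and withdrawal but not discharge. The mITT requires a primary endpoint that the committee could define, so no missing primary outcome is shown.
- A reader might add that palliative discharge should be failed as death is. The SAP groups the two for the discharge outcome and for mortality, not for the antibiotic endpoints.
- A reader might conclude that the rule biases the comparison between arms or inflates the true 48-hour proportion. The SAP gives no Unknown counts by arm. Counting an Unknown as not optimal is a conservative convention, not knowledge of the patient's status. If early discharge differs between arms, the recoding can itself move the arm difference.

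**Conclusion.** The mismatch is on the face of the SAP: the rule's clock and window agree with neither the endpoint, nor the stated baseline, nor the parallel 24-hour rule. For cultures flagged after admission, it cannot classify an Unknown outcome in a patient who leaves less than 48 hours after growth but 24 hours or more after admission. That result is logical and needs no assumed data. That these patients then leave the analysis rests on R's default handling of missing outcomes and on the absence of any other stated rule. The treatment of discharge in the time-to-optimal-treatment analysis points the other way.

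The size is unknown and may be small, because only outcomes the committee left as Unknown are affected. The simulated percentages depend wholly on their assumed distributions. The primary result is unaffected. This should be corrected, but it is not a flaw on which the trial's main conclusion turns.

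**What to change.** Replace the sentence in the 48-hour section with wording such as:

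> *If the 48-hour endpoint is Unknown and the patient was discharged less than 48 hours after first growth (positive culture), it is classified as not optimal, except where optimal treatment was documented before discharge.*

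This puts the rule on the endpoint's own clock and gives the exception a meaning that can be programmed. Report by arm the number recoded and the number still Unknown, so that any remaining loss from the model is visible. Leave the primary endpoint's rule as it is.

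The cost is one sentence, a small change to the derivation code and two counts per arm. The flag and discharge timestamps are already used for the mITT exclusion. The downside is a slightly lower 48-hour proportion. Because the SAP already contains additions made during manuscript drafting, the change should be dated and marked as made before or after results were known.

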## **The total amount of prescribed antibiotics to the patients from enrolment until hospital discharge in defined daily doses (DDD)**

**Derivation**

The defined daily dose (DDD) is a statistical measure of drug consumption, defined by the World Health Organization (WHO), which can be obtained from the WHO Antimicrobial DDD Quick Reference List.

The total amount of prescribed antibiotics (in DDD) is defined as the sum of the DDD’s assigned to each administered drug. The number of DDD’s for each administered drug can be calculated based on the drug name, dose, route, frequency, and the number of days this drug was administered. This information is available in the dataset.

As drugs consumption after hospital discharge was not formally collected, the drug end date will be imputed with the discharge date in case the end date is missing.

**Planned analysis**

The total amount of prescribed antibiotics per patients will be summarized as median (lower and upper quartile). Comparisons between the groups will be based on a linear regression model with treatment as the main covariate and adjustment by the first specimen type and hospital. In case the outcome has a pronounced right skewed distribution, the endpoint will be log-transformed prior to the analysis leading to a comparison of geometric rather than arithmetic means. (the outcome was skewed and therefore log transformed)

As for patients who died early, the amount of prescribed antibiotics is low despite their poor outcome, the endpoint will also be summarized (and informally compared) in survivors only.

## **The total duration of antibiotics and antifungals treatment from enrolment until hospital discharge**

**Derivation**

The total duration of antibiotics (including antifungals) will be derived based on the DRUGS log. As administration of different antibiotics might overlap in time or there may be gaps between different administration episodes, the derivation will first derive start and stop dates of each “antibiotics episode”, i.e. non-overlapping time period where at least one antibiotic was administered. The total duration is then the sum of the duration of all episodes of the subject. As drugs consumption after hospital discharge was not formally collected, the drug end date will be imputed with the discharge date in case the end date is missing.

**Planned analysis**

The duration of antibiotic treatment will be visualized using Kaplan-Meier curves and estimate of median (IQR) of durations in both groups.

Formal comparisons between the two diagnostic arms will be based on the Cox proportional hazards model with the diagnostic arm as the only covariate and stratification by hospital and first specimen type. As for patients who died early, the duration of antibiotic treatment is low despite their poor outcome, the endpoint will also be summarized (and informally compared) in survivors only.

## **Hospital and ICU length stay**

**Derivation**

The duration of hospital stay in days is defined as

Discharge Date – Admission Date +1

The duration of ICU stay is the sum of all stays in ICU wards (including potential ICU re-admissions). The start data of an ICU episode is either the hospital admission day (if the patient was directly admitted to ICU) or the transfer date to an ICU ward. The day of ICU discharge is either the transfer date to the next non-ICU ward or (if no further transfers occur) the hospital discharge date.

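### The Cox comparisons of hospital and ICU stay include time before the SAP's own baseline, which lowers sensitivity if that time is long and variable

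*SAP*

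**What the plan says.** All references are to the SAP.

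- **Baseline** (Analysis population and definition of baseline): "Baseline is defined as the time point when the participant’s first culture flagged positive". The same section excludes from the modified intention-to-treat population "Patients who discharged or died before the culture flagged positive".
- **Hospital stay** (Hospital and ICU length stay, Derivation): "Discharge Date – Admission Date +1".
- **ICU stay** (same derivation): "The duration of ICU stay is the sum of all stays in ICU wards (including potential ICU re-admissions". On where an episode begins: "The start data of an ICU episode is either the hospital admission day (if the patient was directly admitted to ICU"; otherwise it begins at the date of transfer to ICU. No cut at baseline is given.
- **Model** (same section, Planned analysis): Cox regression with the arm as the only covariate, stratified by hospital and first specimen type. Delayed entry is not mentioned.
- **Antibiotic duration**: the heading reads "The total duration of antibiotics and antifungals treatment from enrolment until hospital discharge". The derivation says "The total duration is then the sum of the duration of all episodes of the subject". The only boundary rule is that "the drug end date will be imputed with the discharge date in case the end date is missing". The section on defined daily doses (DDD) has the same window in its heading and the same single rule.
- **A related measure**: time from first specimen collection to discharge is summarised by arm, without a formal comparison.

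**The concern.** A patient enters the analysis only if still alive and in hospital when the culture turned positive. The interval from admission to that moment therefore contains no discharge or death for anyone analysed, and the diagnostic arm cannot shorten it. For ICU, a stay that ended before the positive culture counts in full. These days are nevertheless part of the time axis on which the Cox model ranks patients.

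If the pre-baseline days differ much between patients, they add noise to that ranking. The hazard ratio is then pulled toward 1 and a real effect on stay is harder to detect. A null result on stay could be read as no benefit when the measure was partly fixed before the arm could act.

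The antibiotic endpoints raise a related but weaker point. Their headings limit them to a window starting at enrolment, while their derivations contain no step that applies it.

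**Working it through.** The SAP gives no sample size, effect size or distribution for stay, so there is no figure of its own to reproduce. All inputs below except the two-sided 0.05 level are assumptions.

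**1. What cancels and what does not.** Let T be stay after baseline and L the time from admission to baseline, with L independent of arm. The analysed outcome is L + T.
- *Mean difference:* E(L) cancels. With exponential T, control median 7 days and HR 1.30, the means are 7/ln 2 = 10.10 and 10.10/1.30 = 7.77 days, a difference of 2.33 days. With median 14 days it is 20.20 − 15.54 = 4.66. Simulated differences were 2.30 to 2.34 and 4.59 to 4.73, whatever L was.
- *Cox ranking:* a constant L leaves the order of patients unchanged, so nothing is lost. A variable L reorders them. Because the model is stratified, only variation of L within hospital and specimen-type strata matters.

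**2. Information kept.** Every stay ends in an event, so both clocks have the same number of events and nearly the same variance of the log HR. The information kept is then approximately (log HR from admission / log HR from baseline)².

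Assumptions: T exponential with median 12 days, true HR 1.30, L log-normal, no strata. Results of repeated large simulations (10 × 200,000 patients per setting), rounded:

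| Median of L | Log SD 1: HR | Log SD 1: information | Log SD 0.5: information |
|---|---|---|---|
| 2 days | 1.29 | 92-93% | 99% |
| 5 days | 1.24 | about 68% | 96% |
| 8 days | 1.20 | 47-49% | 91% |

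Check by hand for 8 days, log SD 1: (ln 1.20 / ln 1.30)² = (0.1823/0.2624)² = 0.48.

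The mean of a log-normal is median × exp(SD²/2). An 8-day median with log SD 1 thus means 8 × 1.649 = 13.2 days on average before baseline, against 8 × 1.133 = 9.1 days with log SD 0.5. The first is a demanding scenario.

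**3. Power under a second set of assumptions.** 300 per arm, true HR 1.30, two-sided 0.05, L gamma with coefficient of variation 1, 1,500 runs per setting. Analytic benchmark without L: √(600/4) × ln 1.30 − 1.96 = 3.213 − 1.96 = 1.253, power 0.895.

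| Mean of L | Post-baseline median 7 days: HR, power | Post-baseline median 14 days: HR, power |
|---|---|---|
| 0 (clock at baseline) | 1.30, 0.88 | 1.31, 0.92 |
| 1 day | 1.30, 0.89 | 1.30, 0.89 |
| 3 days | 1.28, 0.86 | 1.29, 0.87 |
| 7 days | 1.23, 0.71 | 1.28, 0.84 |
| 14 days | 1.15, 0.38 | 1.23, 0.71 |

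With L nearly constant at 3 or 7 days, the HR stayed at about 1.30 and power at 0.88 to 0.91. Under no effect, the rejection rate was 0.04 to 0.06 in all settings.

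**4. Antibiotic endpoints, heading against derivation.** Heading: enrolment to discharge. Derivation: sum over all administered drugs (DDD) or all episodes (duration). No step resets a start date that lies before enrolment, and a recorded end date after discharge is not cut, because only missing end dates are handled. Two programmers could produce different outcomes from this text. No arithmetic applies, since the SAP does not say whether the drug log holds pre-enrolment records.

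**The case against.** The strongest reply is that total stay is a coherent outcome in its own right. The hospital and ICU heading does not promise a start at enrolment or baseline, the formula fits the heading, and defining baseline does not oblige every duration to begin there. This stands: the stay definition is not a contradiction, and the change is one of sensitivity. It does not remove the point, because the formally tested outcome still contains days that the arm cannot alter. The summary from specimen collection to discharge starts nearer the intervention but is descriptive only, so it does not fill the gap.

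Three stronger readings are tempting, and the document does not support them.

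- *Immortal-time bias.* A reader might infer bias toward one arm, since the pre-baseline interval is event-free. The interval has the same distribution in both randomised arms, and the simulated type I error stays nominal.
- *Dilution as a certainty.* The loss nearly disappears if pre-baseline time is short or similar across patients, and the SAP gives no distribution. Variation is plausible, since the SAP tabulates transfers from other hospitals, critical-care enrolment and time to growth, but it is not quantified.
- *Pre-enrolment drugs are in the antibiotic outcomes.* The headings fix the window, the content of the drug log before enrolment is not described, and drug use after discharge is said not to have been formally collected. Only a missing truncation step is shown.

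**Conclusion.** The point holds as a possible loss of sensitivity in the Cox comparisons of hospital and ICU stay. Under the assumptions shown, the information kept ranges from about 99% (pre-baseline median 2 days, log SD 0.5) to just under half (8 days, log SD 1). Which end applies depends on a distribution that the SAP does not give. The simulations also assume exponential post-baseline stay, a true HR of 1.30, no censoring and no strata, and they model a single stay from admission. For ICU stay, summed over episodes, they show direction only.

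For DDD and antibiotic duration, what is established is narrower: the derivations do not carry out the window in their headings. Any dilution there is conditional on the drug log holding earlier records.

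All four endpoints are secondary, and the primary endpoint is untouched. This is a cheap improvement and does not threaten the main conclusion.

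**What to change.** 1. **Hospital stay.** For the formal comparison, start the clock at the date-time of the first positive culture and end it at discharge. Alternatively, keep the admission clock and use delayed entry at the positive culture.
2. **ICU stay.** Count only ICU time from the positive culture onward. As the derivation works with ICU admission and transfer dates, state how the day of the positive culture is counted and how patients with no ICU time after baseline are handled.
3. **Total stay.** Keep hospital and ICU stay from admission as a descriptive summary by arm.
4. **DDD and antibiotic duration.** Before summing, cut each drug record to the later of drug start and enrolment and to the earlier of drug end and discharge. Say which timestamp enrolment means, since the SAP does not equate it with the positive culture.

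**Cost.** Some SAP wording and a few lines of derivation code. The SAP's exclusion rule already names date and time fields for growth detection and discharge, and the duration derivation already builds episode start and stop dates. Availability of an enrolment timestamp needs confirming. The downside is that the formal result then describes stay after baseline and not total stay, so reports must label it that way.
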